
##### Qualitative parameters

Inductive Thematic Analysis [73, 74] will be used to analyze themes in the central themes including the target interventions, collaboration, self-monitoring and the process of recovery. These will be coded using labels for participants’, therapists’, and peer counsellors’ words. When interviews are analyzed for the primary themes, the codes of the interviews will be analyzed together to identify the overall emerging sub-themes within the main themes.

### Interim analyses {21b}

N/a. Analyses are conducted at the end of the trial.

### Methods for additional analyses (e.g. subgroup analyses) {20b}

N/a. There is no plan for any additional analyses.

### Methods in analysis to handle protocol non-adherence and any statistical methods to handle missing data {20c}

Missing outcome data in the clinical effectiveness analyses will be handled by the LMM analysis (i.e. given its robustness to missing data) [75]. In the economic evaluations (i.e. CEA and CUA), missing cost and outcome (e.g. QALYs) data will be handled using single imputations nested in 5000 non-parametric bootstraps.

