### Eligibility criteria {10}

We will recruit outpatients with persecutory delusions, independent of DSM classification. The inclusion criteria are main persecutory belief held with at least 60% conviction; low mental wellbeing (score ≤ 43 on the Warwick Edinburgh Mental Well-Being Scale [28], determined using clinical cut-off calculation using the Oxford Feeling Safe sample [5]); and age ≥ 16 years. The exclusion criteria are insufficient competence in the Dutch language to participate in research; currently receiving individual therapy or peer counselling with a frequency of at least one session per month; and unable to understand and sign the informed consent form.

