### Sample size {14}

The sample size for longitudinal intention-to-treat (ITT) analyses with linear mixed models (LMM) was calculated according to the method presented by Liu and Liang (1997) and based on data from previous RCTs [5, 13–15, 24]. Although an ITT analysis with LMM is robust against moderate attrition, we aim to include an additional 10% to compensate for potential dropout. With alpha = 0.05; beta = 0.2; rho = 0.5; 3 repeated follow-up assessments and 10% drop-out; we will need 95 participants in each arm to detect small to medium effects (0.35). Therefore, we aim to include 190 participants.

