## Statistical methods

### Statistical methods for primary and secondary outcomes {20a}

The primary continuous outcomes for mental wellbeing will be analyzed with linear mixed models (LMM) with outcome measurement (at the three follow-up timepoints) as the dependent variable and based on the intention-to-treat (ITT) principle. Baseline values will be added as covariates, time as a categorical variable, and treatment condition as a fixed effect. The regression coefficient of the LMM will be used as the between-group effect size (Feeling Safe-NL vs formulation-based CBTp) since this is the estimated difference in results between the groups.

The secondary continuous outcomes for the persecutory delusion, general paranoid ideation, patient-chosen therapy outcomes and activity will also be analyzed with LMM with outcome measurements (at the three follow-up timepoints) as the dependent variable and based on the intention-to-treat (ITT) principle. Baseline values will be added as covariates, time as a categorical variable, and treatment condition as a fixed effect. Between-group effect sizes (Feeling Safe-NL vs formulation-based CBTp) will be derived from the regression coefficient of the LMM. Outcomes for conviction of the main persecutory delusion (PSYRATS-DS) will also be dichotomized with recovery being defined as conviction falling below 50%. Logistic generalized estimating equations (GEE) with exchangeable correlation structure ITT analysis will be used to examine the effects on dichotomous outcomes, since GEE is reported to be a better estimator of effects in dichotomous outcomes than LMM [66]. Effects for Feeling Safe-NL vs formulation-based CBTp will be computed for “condition” (overall effect) and with interaction effects between time and condition for post-therapy (6-month follow-up; change during the treatment period) and for 12- and 18-month follow-up (change during the follow-up periods).

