#### Mediation

We will also carry out parallel mediation analysis using the PROCESS macro for SPSS [67] to assess the effect of changes in maintenance factors of threat beliefs (e.g. worry, low self-esteem, anomalous experiences, insomnia, safety-seeking behaviours or defences, and trauma imagery), personal recovery and resilience on both mental wellbeing and severity of the persecutory delusion using the assessments at baseline, and 6 (post-therapy), 12- and 18-month follow-up. We will also assess whether the therapeutic relationship mediates changes from baseline to 6 months (post-therapy) and vise-versa.

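### The missing-data rule invokes the LMM, but recovery from the delusion is analysed by an unweighted logistic GEE with no stated baseline covariate, which leaves it exposed to dropout related to baseline severity differently by arm

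*Protocol article*

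**What the plan says.** The protocol article, section {20c}, states a single rule for the clinical effectiveness analyses: "Missing outcome data in the clinical effectiveness analyses will be handled by the LMM analysis (i.e. given its robustness to missing data"). The only other missing-data method, imputation within bootstraps, is reserved for the economic evaluation.

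Section {20a} describes two kinds of model. WEMWBS and the continuous secondary outcomes get an LMM, and for each the article says: "Baseline values will be added as covariates, time as a categorical variable, and treatment condition as a fixed effect". Delusional conviction is also "dichotomized with recovery being defined as conviction falling below 50" per cent, and for this outcome the model changes: "Logistic generalized estimating equations (GEE) with exchangeable correlation structure ITT analysis will be used to examine the effects on dichotomous outcomes". Weighting, imputation and baseline covariates are not mentioned for the GEE.

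Section {10} requires at entry a "main persecutory belief held with at least 60% conviction".

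**The concern.** The rule appeals to a property of a model that is not fitted to this outcome. A correctly specified LMM is estimated by likelihood, so it remains valid when missingness depends on observed data, including the baseline value in the model. An unweighted GEE has no such general guarantee. It tolerates missingness that depends on covariates in its own model, but section {20a} names none beyond time and condition. Calling the analysis intention-to-treat supplies no missing-data method.

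Because everyone enters with at least 60% conviction, baseline recovery status is the same for all patients and cannot serve as a covariate. The continuous conviction rating and the PSYRATS-DS score can, and both should be to hand.

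Recovery is defined as in the earlier Feeling Safe study, so readers will interpret it directly. The arms also differ in contact: Feeling Safe-NL adds about 10 peer-counselling meetings plus joint meetings, and participants know their allocation. Dropout that relates to severity differently by arm is therefore plausible, though nothing in the article shows that it will occur.

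**Working it through.** **The plan's own figure.** Section {14} gives "With alpha = 0.05; beta = 0.2; rho = 0.5; 3 repeated follow-up assessments and 10% drop-out", an effect of 0.35 and 95 per arm. The formula for a time-averaged difference is n = 2(z₀.₉₇₅ + z₀.₈₀)²[1 + (m − 1)ρ] / (m d²). With m = 3, ρ = 0.5 and d = 0.35 it gives 85.4, so 86 per arm. Then 86 × 1.1 = 94.6 (95), or 86 / 0.9 = 95.6 (96). The figure reproduces. No design figure is given for recovery.

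**Assumptions for the check (not in the protocol).** Recovery is 30% with CBTp and 45% with Feeling Safe-NL at each visit, arising from a latent normal score. The true marginal log odds ratio is logit(0.45) − logit(0.30) = 0.647 (OR 1.91).

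**Dropout depending on the last observed recovery status.** The planned GEE was fitted to simulated data with a latent correlation of 0.5. With about 10% or 20% missing at 18 months, the log odds ratio was 0.63 to 0.66, against 0.65 to 0.67 under missing completely at random. Monte Carlo error is about 0.02 to 0.03, so no bias is visible.

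**Dropout depending on baseline, in opposite directions by arm.** Affected patients miss every follow-up, so the GEE has no earlier visit to borrow from. Let b be the standardised baseline score and r its latent correlation with follow-up.

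- Recovery: P(Y = 1 | b) = 1 − Φ((c − r b)/√(1 − r²)), with c = Φ⁻¹(1 − p).
- Dropout: d(b) = expit(logit 0.10 ± 0.8 b), minus for CBTp and plus for Feeling Safe-NL.
- Recovery among retained patients: E[(1 − d)P(Y = 1 | b)] / E[1 − d].

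Direct integration gives 12.2% missing in each arm. The last column holds simulated values at about 13% missing.

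| r | CBTp | Feeling Safe-NL | log OR, integrated | OR | log OR, simulated |
|---|---|---|---|---|---|
| 0.2 | 30.6% | 44.3% | 0.59 | 1.80 | 0.60 |
| 0.3 | 30.9% | 43.9% | 0.56 | 1.75 | 0.53 |
| 0.5 | 31.5% | 43.2% | 0.50 | 1.65 | 0.47 |

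The two sets agree to about 0.03. At r = 0.5 with about 22% missing, the simulated value is 0.39 (OR 1.48).

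**Adding the continuous baseline score (r = 0.5).** Under the same baseline-dependent dropout, the conditional log odds ratio was 0.74 to 0.78, against 0.75 to 0.79 with full data. The bias is gone to within simulation error.

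**Power at N = 190, about 10% dropout, r = 0.5 (150 runs each).**

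| Dropout | Without baseline | With baseline |
|---|---|---|
| Completely at random | 0.79 | 0.91 |
| Baseline-related, opposite by arm | 0.59 | 0.89 |

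The simulation standard error for 0.79 is √(0.79 × 0.21 / 150) ≈ 0.03, so the first contrast is best read as about 10 points. At r = 0.2 to 0.3 the gain is small.

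**The case against.** Four points can be made for the plan.

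- **The familiar mechanism does little harm.** A reader might infer that, because unweighted GEE is often said to require data missing completely at random, loss of unrecovered patients after 6 months would bias the result materially. The planned model does not behave that way. With 19% missing in both arms, the raw 18-month difference among those still observed fell from 0.145 to 0.108, but the exchangeable GEE gave 0.142. Bias seen in a raw available-case comparison is not the bias of this estimator. This stands.
- **Omitting baseline does not in itself bias a randomised comparison.** It costs precision and leaves baseline-related dropout unprotected. This stands too, and so does the caveat that the power gain depends on a baseline correlation the protocol does not give.
- **The detail may sit in an analysis plan or full protocol not shown.** That may be so for GEE covariates and imputation models, on which the article is silent. It does not excuse the rule that is stated, which is written for all clinical analyses and cannot apply to this one.
- **Stakes are modest.** Recovery is an additional dichotomisation within the secondary outcomes, and expected dropout is about 10%.

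A reader might extend the point to the "parallel mediation analysis using the PROCESS macro for SPSS". The article only names the tool there. It does not say how incomplete records will be treated or that imputation will not come first, so no defect can be shown.

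**Conclusion.** The point holds in a limited form. The rule in {20c} does not fit the recovery analysis in {20a}, and a prognostic baseline score that should be available is not planned for that model. The documents do not support a claim that the recovery effect will be biased whenever data are not missing completely at random.

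The exposure is specific: dropout related to baseline severity, and differently so in the two arms. With about 13% missing and strong opposite trends, the log odds ratio moves from about 0.65 to between 0.60 and 0.47, depending on how well baseline predicts follow-up. In the assumed direction the effect is understated; with the directions reversed it would be overstated. These sizes rest on assumed recovery rates, correlations and dropout slopes. If dropout is unrelated to baseline, or related to it alike in both arms, the remaining cost is mainly precision.

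The primary WEMWBS analysis and the continuous secondary outcomes are unaffected.

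**What to change.** 1. Limit the LMM sentence in {20c} to the continuous outcomes.
2. Add the continuous baseline conviction rating or PSYRATS-DS score to the recovery GEE, and say why the dichotomised baseline cannot be used.
3. Multiply impute missing conviction separately by arm, using baseline and all visits, then dichotomise and fit the GEE.
4. State whether the reported odds ratio is conditional on baseline or standardised to a marginal effect.

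The cost is a few sentences and a little analyst time, with no new data. The one downside is that the adjusted odds ratio is conditional, and in the simulations further from 1 than the marginal one, unless it is standardised. It should therefore not be set beside an unadjusted odds ratio from another study without saying so.

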### Plans to give access to the full protocol, participant-level data and statistical code {31c}

Data will be made accessible after an embargo period (completion of PhD project), for verification purposes, safety monitoring, and future research with some restrictions: (1) the approval of the participants as indicated in the consent form, (2) conditions related to data security, (3) quality assessment of the proposed research, (4) collaboration in using the data set. Potential restrictions for data access are evaluated with the privacy experts at the various partner organizations to ensure the protection of the study population, and even if the data are not made available following request, we will make the metadata describing our research publicly available through registration in PURE and any other outputs that do not involve data collected about the participants.

## Oversight and monitoring

### Composition of the coordinating centre and trial steering committee {5d}

The trial is run by the principal investigator, project coordinator (PhD) and trial assessors who meet on a (bi-) weekly basis. There is also a meeting with the trial steering committee every three months including members of the Oxford Cognitive Approaches to Psychosis (O-CAP) research group, trial supervisors, peer counsellors, local principal investigators of the participating mental healthcare institutions, and the randomization bureau.

### Composition of the data monitoring committee, its role and reporting structure {21a}

N/a. The interventions are proven to be acceptable and are used in clinical practice.

### Adverse event reporting and harms {22}

The interventions (formulation-based CBTp, Feeling Safe, and peer counselling) are found to be acceptable and are used in clinical practice. Therefore, no major adverse events related to the interventions are expected. Nor is there any expectation that combining Feeling Safe and peer counselling would result in adverse outcomes. Adverse events reported spontaneously by the participant or observed by the investigators or staff will be recorded. If a serious adverse event occurs, the responsible therapist (and peer counsellor) takes action. The principal investigator will report the serious adverse event through the web portal to the accredited medical ethics committee that approved the protocol within 7 days of first knowledge for serious adverse events that result in death or are life-threatening followed by a period of a maximum of 8 days to complete the initial preliminary report. All other serious adverse events will be reported within a period of a maximum of 15 days after the investigator has first knowledge of the serious adverse events. An elective hospital admission, suicidal thoughts, self-harm, and crisis contacts with mental healthcare professionals will not be considered as a serious adverse event as this regularly occurs within this population. Somatic illnesses will also not be considered as a serious adverse event as this is unrelated to participation in the study.

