### Trial design {8}

A pragmatic single-blind superiority randomized controlled trial with two parallel groups. Patients will be randomized (1:1) to the Feeling Safe-NL Programme or formulation-based CBTp. Measurements are conducted at baseline, 6-, 12-, and 18-month follow-up (see Fig. 1). In both arms, people will receive weekly therapy sessions over a period of 6 months. To support the therapies in both arms, optional self-monitoring is available via brief questionnaires of which the outcomes are visualized. This supports the participant and therapist in monitoring change and shared decision-making.

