### Intervention description {11a}

#### The Feeling Safe-NL Programme

Feeling Safe-NL builds on the Feeling Safe Programme [5] with three adaptions. First, Feeling Safe-NL involves close collaboration between therapists and professional peer counsellors. While therapists work on reducing the maintenance factors of persecutory delusions using targeted CBT and supporting patients to relearn safety, professional peer counsellors focus on addressing personal recovery, together promoting mental wellbeing. Second, Feeling Safe-NL includes trauma imagery as a treatable maintenance factor of threat beliefs [23, 24]. Third, Feeling Safe-NL offers the possibility to self-monitor change to promote people’s agency, shared decision-making and motivation [25, 26]. Feeling Safe-NL involves approximately 20 weekly therapy sessions and 10 bi-weekly individual peer counselling meetings. There are also collaborative meetings (patient, peer counsellor, therapist) to evaluate progress and enhance synergy. This is done at least at the start of the program, near the end of each CBT module and at the end of the program.

Following an introductory meeting with both the therapist and peer counsellor, the therapist and peer counsellor assess the maintenance factors and wishes and needs of the person, respectively. Following this assessment, the therapist offers the patient a menu of relevant CBT modules. Typically, three to four modules are completed, based on patient choice. Modules that can be offered are reducing worry, boosting self-confidence, feeling safe alongside hearing voices, improving sleep, letting go of trauma imagery, and learning to be safe enough through behavioural tests for building safety beliefs. Concurrent to the therapy, the peer counsellor and participant work together according to the sponsor model [31]; the peer counsellor supports the participant during the Feeling Safe-NL Programme based on the participants’ wishes and needs, considering possibilities. The participant and peer counselor work together on personal recovery including identifying and using strengths [22]. The dual approach to improving mental wellbeing is presented in Fig. 2.

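### Self-harm and all somatic illnesses are excluded from serious adverse events without a severity limit, which conflicts with the 7-day reporting rule for fatal or life-threatening events

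*Protocol article*

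**What the plan says.** All the reporting rules stand in one place, the protocol article's section on adverse event reporting and harms {22}.

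- **First exclusion:** "An elective hospital admission, suicidal thoughts, self-harm, and crisis contacts with mental healthcare professionals will not be considered as a serious adverse event". The reason given is "as this regularly occurs within this population".
- **Second exclusion:** "Somatic illnesses will also not be considered as a serious adverse event as this is unrelated to participation in the study".
- **Reporting route:** the principal investigator reports to the ethics committee "within 7 days of first knowledge for serious adverse events that result in death or are life-threatening", and within 15 days for other serious adverse events.
- **Collection:** "Adverse events reported spontaneously by the participant or observed by the investigators or staff will be recorded". No scheduled enquiry about harms is described.

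Planned contact differs between the arms. Under Trial design {8}: "In both arms, people will receive weekly therapy sessions over a period of 6 months". For the experimental arm, Intervention description {11a} says "Feeling Safe-NL involves approximately 20 weekly therapy sessions and 10 bi-weekly individual peer counselling meetings" and adds: "There are also collaborative meetings (patient, peer counsellor, therapist) to evaluate progress and enhance synergy". These joint meetings take place at least at the start, towards the end of each module and at the close of the programme. No session count is given for formulation-based CBTp.

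There is no data monitoring committee {21a}, and no interim analysis is planned {21b}. Therapists and peer counsellors know the allocation; trial assessors do not {17a}.

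**The concern.** Seriousness normally depends on what an event leads to, such as death or a threat to life. Here whole event types are removed by name, on other grounds. The first exclusion rests on how common the events are, which concerns expectedness. The second rests on presumed unrelatedness, which decides causality for every somatic illness before any case is seen. Neither ground makes a life-threatening event non-serious.

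Staff who follow the text could leave a life-threatening act of self-harm or a fatal illness out of the serious adverse event route. That matters more here than in many trials of talking therapies. The Discussion part of the abstract presents this as the first evaluation of peer counselling combined with a CBT-based programme for this problem. With no data monitoring committee, reporting to the ethics committee is the main external safety check that the article describes.

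The second, lesser concern is the count of recorded events. If recording depends on what patients mention and staff notice, the arm with more meetings has more occasions to record an event.

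**Working it through.** **1. The two sets of statements side by side.** The harms section gives no figure to reproduce, so the main check is on the text.

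| Event | Under the exclusions | Under the 7-day route |
|---|---|---|
| Life-threatening self-harm | Not serious (no severity limit) | Life-threatening, so reportable if it counts as serious |
| Fatal somatic illness | Not serious (declared unrelated) | Fatal, so reportable if it counts as serious |
| Suicidal thoughts or crisis contact, no serious outcome | Not serious | Not engaged |
| Unplanned psychiatric admission | Not excluded by the admission wording, which covers elective admissions only | Depends on outcome |

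The first two rows can be read in two ways. Either the exclusions come first and the event never enters the 7-day route, or the event is both excluded and reportable. The first reading loses the report; the second leaves staff with two rules. Both need a change of wording.

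**2. Planned contacts in the 6-month treatment period.**

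- Feeling Safe-NL: about 20 + 10 = 30 individual meetings. With three modules, the joint meetings number at least 1 + 3 + 1 = 5. The article does not say whether they are separate from the sessions, so 30 to 35 is assumed.
- CBTp: weekly over 6 months, count not stated. Assumed 20 (as in the other arm) to 26 (every week).
- Simple ratios of individual meetings: 30/20 = 1.50; 30/26 = 1.15.

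**3. What unequal contact could do to recorded counts.** Assume equal true event rates, event times spread evenly over the K contacts, and a chance q at each contact from the event onwards that it is mentioned or observed. The share of events recorded is

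R(K, q) = (1/K) × Σ (k = 1 to K) [1 − (1 − q)^k].

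Example with q = 0.05: R(30) = 0.503 and R(20) = 0.391, so the ratio is 0.503/0.391 = 1.29.

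| q per contact (assumed) | Lowest ratio (30 v 26) | Highest ratio (35 v 20) |
|---|---|---|
| 0.02 | 1.12 | 1.56 |
| 0.05 | 1.09 | 1.40 |
| 0.10 | 1.05 | 1.24 |
| 0.20 | 1.02 | 1.10 |
| 0.50 | 1.01 | 1.02 |

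The documents do not give q. Every ratio exceeds 1, so under this model the distortion runs only towards more recorded events in Feeling Safe-NL.

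**4. Dilution over the whole trial.** The extra contact falls in 6 of the 18 months. Suppose events are spread evenly over 18 months, and in the last 12 both arms record the same share as CBTp did during treatment. The overall ratio is then (ratio + 2)/3. The largest value becomes (1.56 + 2)/3 = 1.19 and the smallest (1.01 + 2)/3 = 1.00.

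**The case against.** Several points on the other side are sound.

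- The exclusions concern the serious category, not recording. Self-harm, suicidal thoughts and crisis contacts can still be recorded as non-serious adverse events, so a reader who infers that these harms are lost goes too far.
- The exclusions apply equally to both arms. They make the serious-event record incomplete; they do not by themselves tilt the comparison.
- Only elective admissions are excluded, and suicide is not named.
- Observation by investigators is a recording route as well. Blinded assessors see both arms on the same schedule, standard care is monitored by the research team {11d}, and the TIC-P collects healthcare use equally in both arms.
- The steering committee, set up in place of a data monitoring committee, meets every three months.
- A condensed article may leave the definition of seriousness to the full protocol.

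The last point does not remove the main one. The article does not merely omit a definition: it states unqualified exclusions and gives reasons for them. If the full protocol has a qualifier, the article misreports it; if not, the gap is real.

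A reader might also infer that the harms comparison is biased by a factor of 1.5, or that no difference in either direction could be interpreted. The documents support neither. The 1.5 needs a CBTp count of 20 that is nowhere stated, and detection strictly proportional to contacts. The modelled distortion has one direction, so a lower recorded count in Feeling Safe-NL would stand despite it.

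**Conclusion.** The main point holds on the text alone and needs no numerical assumption: the unqualified exclusions and the rule for fatal or life-threatening events must be reconciled, and the advance ruling on somatic illness is not a sound basis for classifying individual cases. What is at stake is the completeness of serious adverse event reporting. The primary analysis is untouched.

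The secondary point is a possible distortion of unknown size. During treatment, illustrative ratios run from 1.01 to 1.56, given 30 to 35 contacts against 20 to 26 and a detection chance of 0.02 to 0.50 per contact, all of which are assumptions. If detection is high, as one would expect for grave events, the effect is negligible. This justifies caution when counts are read by arm; it does not show that the comparison is biased.

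**What to change.** 1. State that the exclusions cover only events that meet no seriousness criterion, so that fatal or life-threatening events stay reportable whatever their type.
2. Replace the blanket rule that somatic illness is unrelated with case-by-case assessment.
3. Tabulate self-harm, suicidal thoughts, crisis contacts and somatic illnesses by arm as adverse events, with numbers of events and of patients, and note the unequal contact beside the table.
4. Use the TIC-P data at 6, 12 and 18 months as a check on crisis contacts and admissions. It is described as a costing instrument, and self-harm or suicidal thoughts without service use will not show in its healthcare-use data, so it is only a partial check.

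New harms questions partway through are not needed for this. Recruitment began in March 2022, and adding them now would mix two ways of finding events.

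The cost is an amendment through the ethics committee, somewhat more serious adverse event reports, one extra table, and one look back at events already recorded under the present wording.
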